### Patient adherence

Following recent recommendations for enhancing participant engagement in clinical studies [62], every participant has one contact person throughout the study. Every participant is welcomed by one of the principal investigators at the t0 visit, and this individual contact person is present at every following study visit, if possible. All participants will receive an information folder containing an overview of the study, contact information, and a schedule of appointments, where they can store all study documents (such as study information, insurance information, and consent forms). The participants will be reminded of their following appointments by email 1 week before the scheduled date. At every appointment and during each contact, the participant’s individual contact person will actively seek out any open questions and remarks and will provide assistance accordingly. At the end of the study, participants will receive individual feedback about their neuropsychological test performance, if desired, and a travel cost subsidy (max. € 150 for individuals with iRBD, € 60 for HC individuals). If, for whatever reason, complete study adherence is not possible, an effort will be made to collect as much data as possible from the respective participant.

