### Randomization and blinding

Randomization in CogTrAiL-RBD is based on a minimization procedure designed to minimize differences between the early intervention group and the delayed-start control group in age, sex, and premorbid IQ [63]. The minimization randomization is implemented using the R package *Minirand* [64]. We aim at a 1:1 ratio of the number of subjects in the early intervention group and the delayed-start control group. The covariates age, sex, and premorbid IQ will be equally weighted (1/3 each). The participants with iRBD will be consecutively randomized following the clinical and neuropsychological t0 baseline assessment by a person not involved in t1 to t4 data collection, preferably by their individual contact person, who will assign the participants to the intervention and monitor their training progress.

The assessments will be double-blinded at t0 baseline (i.e., randomization will be carried out after the t0 baseline assessment) and single-blinded at t1 to t4 posttests and follow-ups (i.e., outcome assessors do not know the participant’s group allocation). Any violations of blinding will be documented, e.g., if participants do not fully comply with the explicit instruction not to give any clues about their experimental group allocation to the outcome assessors.

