Overall, under careful consideration of the inclusion and exclusion criteria, the risks of the study are minimal. Participants will be informed about possible risks and adverse events (AE) at their t0 visit. Participants can withdraw from the study at any point without providing a reason and without facing any disadvantages. No written explanation is required, and a verbal statement is sufficient for dropout. Outcome assessors and study coordinators will be instructed to monitor and document all AE throughout the study. If a serious AE occurs, the study physician will be consulted and asked to assess whether or not a causal relationship with the intervention is considered possible. Beyond the trial, participants will be part of the local iRBD cohort, receiving access to approximately yearly clinical visits and additional visits as needed.

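### Outcome assessors who must stay blind are also told to document adverse events, which puts the masking of the primary outcome at risk at t1 and t2

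*Protocol article*

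**What the plan says.** All references are to the protocol article.

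- **Randomization and blinding.** The assessments are "single-blinded at t1 to t4 posttests and follow-ups", which the article explains as meaning that "outcome assessors do not know the participant’s group allocation". Randomization is done "by a person not involved in t1 to t4 data collection", and "preferably by their individual contact person, who will assign the participants to the intervention and monitor their training progress". Participants are told not to reveal their group, and breaches are logged: "Any violations of blinding will be documented, e.g., if participants do not fully comply with the explicit instruction not to give any clues".
- **Expected harms and adverse events monitoring.** "Outcome assessors and study coordinators will be instructed to monitor and document all AE throughout the study". If an event is serious, the study physician judges whether the intervention may have caused it.
- **Patient adherence.** After t0, "this individual contact person is present at every following study visit, if possible". At each appointment and contact, "the participant’s individual contact person will actively seek out any open questions and remarks and will provide assistance accordingly".
- **Computerized multi-domain cognitive training.** The contact person checks training progress weekly online. Participants' queries are answered by telephone or email.

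**The concern.** Participants know their arm because the control group receives nothing before t2. For the primary outcome, that leaves the assessor's ignorance of the arm as the only masking. The executive composite is built from tests that an examiner gives face to face, so an examiner who knows the arm could influence instruction, encouragement or scoring.

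The adverse-event duty works against this. Someone who documents adverse events hears what has happened to the participant since the last visit. At t1 and t2 that history includes training sessions, the lifestyle booklet and the activity diary in one arm only. The disclosure would then be prompted by the assessor's own task, not by a careless participant. These two visits are the post-baseline points of the primary model, in the only phase for which the trial is powered. A leak that favoured the early arm would bias the main comparison.

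**Working it through.** **Step 1. Who can learn the arm, and when.**

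| Role | Assigned task | Knows the arm at t1/t2? |
|---|---|---|
| Participant | Trains before t1 (early) or after t2 (delayed) | Yes |
| Contact person | Preferably randomizes; monitors training weekly; attends later visits if possible | Normally yes |
| Outcome assessor | Gives the tests; must not know the arm | Must be no |
| Outcome assessor, same people | Monitors and documents all adverse events, with study coordinators | Still must be no |

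The last two rows give the same people two tasks. The article says nothing about how the second is kept from defeating the first.

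**Step 2. Do the stated safeguards cover this route?**

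- Keeping the randomizing person out of t1 to t4 data collection governs who tests. It does not govern what the tester hears when taking adverse-event reports.
- The instruction to participants asks them not to volunteer clues. A participant who tells the assessor about an adverse event may have to mention training to describe it.
- Logging violations records a leak after it has happened. It does not prevent one.

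**Step 3. Does an adverse-event report identify the arm?** Not by itself. The only expected effect, mild transient fatigue, is listed for the assessments and accelerometry as well as for the training and lifestyle module. Both arms have the first two; only the early arm has the other two before t2. The context of a report would reveal the arm (for example, tiredness after training days), not the symptom.

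**Step 4. The contact person.** Attending the visit is not the same as attending the test session. The contact person is meant to attend in both arms, so presence alone reveals nothing. What remains is a conversation about training within the assessor's hearing. The text neither describes nor excludes this.

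**Step 5. Size.** The document gives no rate of unblinding and no effect of unblinding on scores, so there is no plan figure to reproduce for this point. The following shows only how sensitive the primary comparison would be, under assumed biases.

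Inputs from the sample-size section:

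- 64 per group for d = 0.5 (power recomputed as 0.801)
- factor √(1 − 0.8²) = 0.6, so 64 × 0.6 = 38.4, stated as 38 per group
- 76/0.95 = 80

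Formulas: SE = √(factor × 2/38), and two-sided error = 1 − Φ(1.96 − b/SE) + Φ(−1.96 − b/SE), where b is the assumed average between-arm bias in SD. The plan's factor of 0.6 and the usual ANCOVA variance factor 1 − 0.8² = 0.36 are both shown. Which factor is right is a separate matter.

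| Assumed b (SD) | Error, factor 0.6 (SE 0.178) | Error, factor 0.36 (SE 0.138) |
|---|---|---|
| 0 | 5.0% | 5.0% |
| 0.05 | 5.9% | 6.5% |
| 0.1 | 8.7% | 11.2% |
| 0.2 | 20.3% | 30.6% |
| 0.3 | 39.3% | 58.7% |

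This is a normal approximation to a single adjusted comparison, not the planned mixed model. It shows that a modest bias would matter if one existed. It is no evidence that one does.

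**The case against.** The strongest reply has four parts.

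1. **The sections are compatible.** A reader might infer that having the contact person at later visits contradicts the rule keeping the randomizing person out of data collection. It does not: one person can support the participant while another tests. The wording is also conditional, the contact person attends in both arms, and training queries have a telephone and email route. This stands, so the contact person's attendance is not an error.
2. **The adverse-event duty is milder than it looks.** It covers all events in both arms, is shared with coordinators, speaks of monitoring and documenting and not of active questioning, and leaves causality of serious events to the study physician. All true. But sharing the duty does not remove it from the assessors, and documenting an event still means hearing about it.
3. **The outcome is fairly robust.** The components are fluency, trail making, Stroop interference and a reasoning subtest. Scores are timed, counted or keyed, and the assessors are trained and the scoring double-checked. This limits the room for bias but does not remove the examiner's influence on administration.
4. **The article condenses a longer protocol.** Visit order and staff instructions may be set out there. That disposes of any complaint about missing operating detail. It does not dispose of the adverse-event point, which concerns a task the article expressly assigns.

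**Conclusion.** The point holds in limited form. The article gives adverse-event documentation to the people whose blindness the primary outcome depends on, at visits where only one arm has trained. The safeguards it names do not close that route. This puts the masking at risk. A reader might go further and conclude that the blinding is broken, or attach a figure to the resulting bias. The documents support neither, because they report no leak and give no rate or effect of unblinding. The table above rests wholly on assumed biases.

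The judgement assumes that assessors take adverse-event reports from participants at t1 and t2, as the instruction implies, and that no unshown procedure keeps this apart from testing. It is a worthwhile, low-cost improvement. It affects neither the sample size nor the planned analysis.

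**What to change.** - In the section on expected harms and adverse events, assign adverse-event enquiry and documentation at t1 and t2 to the study coordinators or the contact person, after testing and away from the assessor. Limit assessors to recording acute events during the test session. The study physician's role for serious events stays as it is.
- Use one standard set of adverse-event questions in both arms, because the staff asking may know the allocation.
- In the section on patient adherence, add that any conversation about training takes place outside the test session and out of the assessor's hearing.

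The cost is wording, a staff instruction and slightly more coordination per visit, with no new staff. The trade-off is that unblinded staff may collect adverse events, which the standard questions mitigate. At the article's status date 55 of the planned 80 participants were enrolled, so at least 80 − 55 = 25 still had both visits ahead of them. For visits already completed, the log of blinding violations can be reported by arm.

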### Randomization and blinding

Randomization in CogTrAiL-RBD is based on a minimization procedure designed to minimize differences between the early intervention group and the delayed-start control group in age, sex, and premorbid IQ [63]. The minimization randomization is implemented using the R package *Minirand* [64]. We aim at a 1:1 ratio of the number of subjects in the early intervention group and the delayed-start control group. The covariates age, sex, and premorbid IQ will be equally weighted (1/3 each). The participants with iRBD will be consecutively randomized following the clinical and neuropsychological t0 baseline assessment by a person not involved in t1 to t4 data collection, preferably by their individual contact person, who will assign the participants to the intervention and monitor their training progress.

The assessments will be double-blinded at t0 baseline (i.e., randomization will be carried out after the t0 baseline assessment) and single-blinded at t1 to t4 posttests and follow-ups (i.e., outcome assessors do not know the participant’s group allocation). Any violations of blinding will be documented, e.g., if participants do not fully comply with the explicit instruction not to give any clues about their experimental group allocation to the outcome assessors.

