### Sample size and power calculation

To determine an adequate sample size, an a priori power analysis was conducted with G*Power [57] (http://www.gpower.hhu.de). The study will be powered to reliably detect behavioral effects in the domain of executive functions (the primary outcome) in the first parallel-group phase of the randomized controlled trial in individuals with iRBD. According to two meta-analyses on cognitive training in healthy older adults [58] and individuals with PD [36], we expect a medium effect size (Cohen’s *d* = 0.5) in the domain of executive functions. With a two-sided *α*-level of 0.05 and 80% power, the minimum sample size comparing the difference between two independent groups (allocation ratio 1:1) with a *t*-test is *N* = 128 (i.e., *n* = 64 per group).

We applied the correction formula of Borm et al. [59], acknowledging the increase of precision in estimating a treatment effect when the correlation between the outcome measure at baseline and retest ($$\rho$$) by ANCOVA is considered: *n*_cor_ = *n**$$\sqrt{1-{\rho }^{2}}$$. A meta-analysis [60] on the reliability of neuropsychological measures identified particularly high correlations between baseline and retest measures of executive functions (Pearson’s *r* ≥ 0.80). Following, the G*Power estimate of *n* = 64 per group was corrected by the factor $$\sqrt{1-{0.8}^{2}}=0.6$$, resulting in a minimum sample size of *n*_cor_ = 38 per group, i.e., a total sample of *N*_cor_ = 76. The estimated dropout rate for the first parallel-group phase of the randomized controlled trial of the present trial is 5%, based on previous experiences with a similar intervention in individuals with PD [61]. Following, we aim to recruit *N* = 80 (= 76/0.95) individuals with iRBD for the present trial.

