#### Neuropsychology and motor assessments

All subjects will undergo clinical and neuropsychological assessments, including paper–pencil cognitive and motor evaluations. The in-person assessments take around 2.5 h to complete, including a short break according to the participant’s needs. The test battery will be administered by psychologists or graduate students of Psychology or Medicine at all time points. The outcome assessors will be thoroughly trained in administering and scoring the assessments. Following the in-person assessments, participants digitally fill out questionnaires on various non-motor symptoms, quality of life, and lifestyle activities, which are sent to them via SoSci Survey (SoSci Survey GmbH, Munich, Germany). An automatic reminder email is sent to the participants, if they do not complete the questionnaire within 1 week of their study visit. A complete list of all cognitive assessments, motor evaluations, and questionnaires, including references, is presented in Table 1. Parallel test forms are used if available (i.e., alternating between time points). Test scores are standardized into *z*-scores, percentage ranks (PR), or *T*-scores using published normative data, as available. All evaluations are double-checked and digitalized using the four-eye principle. All standardized scores are transformed into *z*-scores during data preprocessing to create the domain composite scores. Table 1 provides an overview of the assignment of cognitive tests to the respective domains.

**Table 1 Tab1:** Neuropsychological and motor assessments in CogTrAiL-RBD

Domain	Abbreviation	Assessment	Reference	Baseline	Posttest I and II	Follow-up I and II

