For the analysis of training effects in the primary and secondary outcomes, linear mixed effects (LME) models will be used. Dependent variables are the respective primary or secondary outcome measures. All dependent variables are assessed at three points of time. The LME models include time (t0, t1, t2), group (early intervention group and delayed-start control group), and the interaction between time and group (time*group) as fixed factors. Furthermore, participants and time are included as random factors. Models will be estimated using the *lmer()* function of the *lme4*-package employing restricted maximum likelihood estimation [119]. Model fit will be evaluated using marginal *R*^2^, which considers the variance of the fixed effects only, and conditional *R*^2^, which accounts for both fixed and random effects. *t*-Tests will be conducted to assess the significance of single coefficients. For the interaction effects, relative effect sizes with 95% confidence intervals will be reported and defined as the difference of the mean change over time in the early intervention group minus mean change over time in the delayed-start control group divided by the pooled baseline standard deviation of the cohort. Within the analysis of training effects, we will pursue an intention-to-treat approach. No imputation methods will be used, as one strength of LME models is their ability to deal with unbalanced designs, for example, due to missing values in longitudinal data.

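### The minimisation factors are missing from the mixed models, which makes standard errors slightly conservative, and only as far as those factors predict change

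*Protocol article*

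**What the plan says.** In *Randomization and blinding*, the protocol article describes a minimisation procedure "designed to minimize differences between the early intervention group and the delayed-start control group in age, sex, and premorbid IQ", with equal weights: "The covariates age, sex, and premorbid IQ will be equally weighted (1/3 each".

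In *Statistical analyses*, the model for the primary and secondary outcomes is set out as follows: "The LME models include time (t0, t1, t2), group (early intervention group and delayed-start control group), and the interaction between time and group". On random effects it adds: "Furthermore, participants and time are included as random factors". Age, sex and premorbid IQ do not appear, and no reason is given. The effect size for the interaction is "defined as the difference of the mean change over time in the early intervention group minus mean change over time in the delayed-start control group". That difference is then scaled by the baseline SD of both arms combined.

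The same section says that the article reports the analyses of the primary and secondary neuropsychological and motor outcomes for the parallel-group phase. Separate plans are announced only for exploratory outcomes and exploratory analyses.

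**The concern.** Minimisation makes the arms more alike on chosen factors than chance would. If the analysis ignores those factors, it counts their variation between people as noise that could have differed between arms, although the allocation largely prevented this. Where the factors predict the quantity being compared, the model-based standard error then exceeds the true sampling variation, and the test rejects less often than its nominal level.

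What is at stake is precision, not false positives: confidence intervals somewhat too wide and p-values somewhat too large, in a trial of 80 people. How much depends on what is being compared, and here that is change, not level.

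**Working it through.** **1. The plan's own figures.** Inputs from *Sample size and power calculation*: d = 0.5, two-sided α = 0.05, 80% power, 1:1 allocation, baseline-retest correlation 0.8, 5% dropout.
- The exact two-sample t calculation gives 64 per arm.
- 64 × √(1 − 0.8²) = 64 × 0.6 = 38.4, taken as 38; 2 × 38 = 76; 76/0.95 = 80.

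The arithmetic reproduces (whether that correction factor is the right one is a separate question). No step uses age, sex or IQ, so the omission changes no stated figure.

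**2. What cancels.** Let a factor x shift a person's score by b·x at every visit. In the change from t0 to t1, b·x drops out. Only a part c·x that appears after baseline remains. With outcome SD 1 and correlation 0.8:
- variance of change = 2(1 − 0.8) = 0.4
- SE of the difference in mean change at 38 per arm = √(0.4 × 2/38) = 0.145
- SE after adjustment ≈ 0.145 × √(1 − R²), where R² is the share of **change** variance that the factors explain.

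| R² of change (assumed) | SE ratio | Power at 38 per arm |
|---|---|---|
| 0 | 1.000 | 92.5% |
| 0.05 | 0.975 | 93.7% |
| 0.10 | 0.949 | 94.8% |
| 0.20 | 0.894 | 96.7% |

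**3. Mixed models on simulated trials.** There were 76 participants, three visits and correlation 0.8. Assumptions: minimisation with median splits for age and IQ and a biased coin of 0.8; factors explaining 30% of the variance in level; a REML model with a random intercept only, so the plan's random time term is not represented. Each scenario has 40 data sets. Mean SE of the t1 time*group coefficient:

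| Scenario | As planned | + main effects | + factor-by-time |
|---|---|---|---|
| Factors predict level only | 0.1419 | 0.1419 | 0.1425 |
| Factors also explain 10% of change | 0.1428 | 0.1428 | 0.1379 |

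Main effects alone give a ratio of 1.000 in both rows, and 0.999 when 4 of 76 people are lost after t0. Factor-by-time terms give 0.966 in the second row, and 0.973 with that loss.

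**4. Are the reported SEs right?** The t0-to-t1 change contrast was analysed without the factors in 3,000 minimised trials per scenario. The Monte Carlo error of a 5% rate is √(0.05 × 0.95/3000) ≈ 0.4 percentage points.

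| R² of change | Model SE | Empirical SE | Type I error |
|---|---|---|---|
| 0 | 0.1443 | 0.1444 | 4.9% |
| 0.10 | 0.1446 | 0.1381 | 3.9% |
| 0.30 | 0.1451 | 0.1308 | 3.2% |

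At 10% the model SE is 0.1446/0.1381 = 1.047 times the true one. With the factors in the model it is 0.1379 against an empirical 0.1367, and type I error is 4.8%.

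**5. Is the balance lost?** At 10% of change variance, the empirical SE of the unadjusted contrast is 0.1381 under minimisation and 0.1472 under a purely random split. The design gain is in the estimate even without adjustment; the reported SE fails to credit it.

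**The case against.** Four arguments weigh against the point.

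- **The effect may be nil.** Nothing in the article shows that the three factors predict change, and it does not say that they were chosen as prognostic. Scores are standardised "using published normative data, as available", which may already remove part of their influence; which factors the norms cover is not stated. This stands, and it is why the range must start at zero.
- **Adjustment is not free.** With three visits it adds three main effects and six interaction coefficients in about 76 people. This stands, but if the factors predict level only the SE moves from 0.1419 to 0.1425, about half a percent.
- **Power is not short on the plan's own inputs.** At correlation 0.8 the change contrast already has 92.5% power, so the gain is modest. This stands too. At an assumed correlation of 0.6 that power would be about 67%, and small gains would matter more.
- **The article is condensed, and covariates are often left to an analysis plan.** This carries less weight, because the section sets out the fixed effects explicitly and says that it reports these very analyses.

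A reader might infer that leaving out the factors throws away the balance gained by minimisation, or that the standard errors are simply too large. Neither follows. The balance still reduces true sampling variation, and with factors that predict only level the reported SE is correct. The marked inflation belongs to a post-test comparison without baseline (model SE 0.229, empirical 0.202, type I error 2.4%), which is not the planned analysis.

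**Conclusion.** The mismatch between allocation and analysis is real and stands in the text. Its effect is minor and in the safe direction. If the factors explain none of the variance in change, the planned SE and test are correct. If they explain 10%, adjustment cuts the SE by 3 to 5% and the unadjusted test runs at about 4% rather than 5%.

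These sizes rest on assumptions that the article cannot confirm: the share of change variance explained (0 to 10%), a correlation of 0.8 across visits, the minimisation settings used, and a random-intercept model in place of the plan's random effects. The documents do not support a claim of invalid inference or of a sample size made wrong by this omission. The point is worth acting on because the remedy costs almost nothing.

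**What to change.** Before the analysis that follows the last t2 visit, specify that the primary and secondary models include age and premorbid IQ as continuous terms and sex, each with its interaction with time. The interactions are essential, because main effects alone do not alter the time*group standard error. Take the numerator of the reported effect size from the adjusted time*group contrast, and keep the model without the factors as a sensitivity analysis. If the authors prefer to omit the factors, a sentence giving the reason would do.

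The cost is one line per model and nine coefficients. No new data are needed, since minimisation required all three values for every randomised participant. The downside is a few degrees of freedom and an SE about half a percent larger if the factors predict level only.
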